### Measures

#### Autism Surveillance Pathway (ASP)

The parent completed developmental surveillance instruments are listed below.

“Learn The Signs Act Early” (LTSAE) developmental checks as recommended by the Centre for Disease Control (41) are used to monitor children's early development in the domains of social and emotional, language/communication, cognitive (learning, thinking, problem-solving), and movement/physical development. These developmental milestone checklists are available for children aged 2 months to 5 years, and the checklists for 18–23 and 24–29 months are included in this study. The aim of the LTSAE used by the NSW Health as part of the developmental surveillance program is to engage families and encourage parents/caregivers and health service providers to learn/monitor the signs of healthy development.

The Parents' Evaluation of Developmental Status (PEDS) (42) is designed for children from birth to 8 years of age and consists of ten questions asking parents/caregivers about concerns they have in domains including global/cognitive, expressive language and articulation, receptive language, fine and gross motor, behavior, self-help, socialization, and academic. It is widely used in Australia and is the first-line developmental surveillance tool used in state-based programs in most states in Australia and internationally. Screening test characteristics are over 70% for sensitivity and specificity for developmental concerns.

The Quantitative Checklist for Autism in Toddlers-10 item (Q-CHAT-10) is an ASD-specific ten-item tool to aid the decision making for primary care professionals about whether to refer a child for a full diagnostic assessment for ASD. The ten most accurate items from the original Quantitative Checklist for Autism in Toddlers (Q-CHAT) (43) were identified and included in this shortened version. Using a cut-off point of three, the Q-CHAT-10 has sensitivity of 0.91, specificity of 0.89, positive predictive value (PPV) of 0.58, and internal consistency of 0.85, when used in a *clinical population*; its utility when used in community-based samples has not been reported (44).

The Ages and Stages Questionnaire: Social Emotional scale (ASQ:SE) (45) is a screening tool focusing on the social and emotional behavior of children aged 6- to 60-months. This study uses the *18- and 24-month questionnaires*. Parents are asked a series of questions regarding their child's self-regulation, communication, autonomy, compliance, adaptive functioning, affect, and interaction with people. The ASQ (46) and the ASQ:SE have sound psychometric properties and the ASQ/ASQ-SE is the recommended developmental surveillance and health monitoring program in all Australian States with the exception of Victoria [where the Brigance Screens is used in its place (47)] for identification of developmental problems. The measure has been shown to have good reliability as a developmental screener globally with Cronbach's alpha of 0.79 for the total score and 0.61–0.74 for all the domains indicating acceptable reliability (48).

GP/PN completed autism developmental surveillance instrument:

The Social Attention and Communication Surveillance – Online (SACS Online) tool (34–37) is a professional observational tool intended for use in 11- to 30-month-old children, with the 18- and 24-month versions in use for this current study. Originally designed for use by maternal and child health nurses it is also suitable for use by other primary health professionals. The tool consists of five “key” behavioral items per age group plus additional items, with professionals asked to note whether the child is displaying typical or atypical behavior for each item. Where a child is noted to have atypical behavior for three of the five “key” items, it is recommended that they be referred for further assessment. Study results have indicated that the SACS tool and its revised version have high sensitivity (82–84%), specificity (99–99.8%), PPV for autism (81–83%; and 100% for *any* language/developmental delay or condition), and negative predictive value (99%), making it highly suitable for use in primary- and community-health and early childhood settings (34, 36). In the current study, GPs and PNs will be provided with access to the training modules in the use of the SACS Online tool via their online study portal, which they will complete prior to commencing child assessments.

#### Surveillance as Usual (SaU) Pathway

GPs and PNs will use a standard template to log the methods and tools used by the GP to assess children to be at high likelihood for autism, including details such as what concerns were raised and by whom, the assessment(s) completed, the reason for the assessment, the GP's findings, and any referrals and/or recommendations made.

### Procedures

#### Autism Surveillance Pathway (ASP)

Parents/caregivers in the ASP arm will complete electronic versions of a participant information and consent form, a brief demographic questionnaire, in addition to the LTSAE, PEDS, and Q-CHAT-10 in the GP clinic waiting room. REDCap (NSW site) and Salesforce (VIC) will be used to manage the completion of these forms and questionnaires. An embedded algorithm on the REDCap and Salesforce platforms will score the parent responses to identify children as having developmental risk and/or high likelihood for autism, and this information from the initial assessments will be passed on automatically to the child's GP (and PN if applicable). During the consultation, the GP (or PN) will also complete the SACS Online using the Salesforce platform at both NSW and VIC sites. The ASQ:SE will be completed by parents/caregivers of children identified as having any developmental concern following completion of the LTSAE, PEDS, Q-CHAT-10, and/or SACS Online. Children will be determined as having a “high likelihood” for ASD if they: (a) are identified as “high likelihood” for autism by either the Q-CHAT-10 *or* the SACS Online assessment (regardless of the outcome of the other tools); or (b) are identified as at developmental risk by LTSAE and/or PEDS *and* ASQ:SE (but were found not at high likelihood for autism by Q-CHAT-10 and SACS Online).

#### Surveillance as Usual (SaU) Pathway

Parents/caregivers of children in the SaU arm will complete electronic versions of the participant information and consent form and a brief demographic questionnaire. GPs (or PNs) will record any developmental screening method(s) used during the consultation using the standard template and the child's developmental risk status (i.e., high likelihood of autism).

### Phase 2 – 24-Month Assessment Protocol

#### Measures

##### ASD Traits

The Autism Diagnostic Observation Schedule-2 (ADOS-2) (49) will be used to confirm a diagnosis of ASD. The ADOS-2 is a semi-structured, standardized diagnostic observational assessment of social interaction, communication, play, and imaginative use of material for individuals suspected of having autism. The ADOS-2 module administered (by the trained clinician or researcher) is determined by the child's age and expressive language ability. The Toddler Module is for children aged between 12- and 30-months and will therefore be administered in this study (50, 51).

The Autism Diagnostic Interview-Revised (ADI-R) (52) is diagnostic, semi-structured, extended parental/caregiver interview including ninety-three items assessing reciprocal social interaction, communication, play, and repetitive, restricted, and sensory behaviors and interests. Test-retest and inter-rater agreement (intra-class correlations ≥ 0.92), and discriminant validity between autistic and non-autistic individuals for each of the domains are all excellent (52).

##### Developmental Skills

The Mullen Scales of Early Learning (MSEL) (53) is a standardized measure of nonverbal and verbal development in children from birth through to 68 months of age. The MSEL consist of five subscales: gross motor, fine motor, visual reception, receptive language, and expressive language. For each domain, raw scores and corresponding age equivalence scores are recorded. The gross motor scale will not be utilized in this study. The MSEL has excellent test-retest and inter-scorer reliability for children aged ≤ 24 months (*r* ≥ 0.82) (53).

##### Child Behavior

The Vineland Adaptive Behavior Scales third edition (VABS-3) (54), a parent/caregiver completed questionnaire, will be used to assess adaptive/functional skill development. It provides a measure of adaptive behavior in four broad domains of communication, daily living skills, socialization, and motor skills. The VABS-3 has sound psychometric properties with internal consistency of 0.90–0.98, test- re-test reliability of 0.80–0.92 and inter-rater reliability of 0.79 (55).

Parents and caregivers will also complete the Sensory Experiences Questionnaire - short form (SEQ) (56) and the Infant/Toddler Sensory Profile (ITSP) (57) to assess the child's sensory profile through understanding their response to a range of sensory experiences. The SEQ has good internal consistency (α = 0.80) (56) and excellent test-retest reliability (intra-class correlation = 0.92) (58). In seven to 36 month olds, the ITSP has poor to good internal consistency (α = 0.42–0.86) for item groupings, and acceptable to good test-retest reliability (intra-class correlation = 0.74–0.86) across sections and quadrants (59).

### Procedure

Parents/caregivers of children in both the ASP and SaU arms who are identified as having a “high likelihood” for autism at 18- or 24-months will be invited by the researchers for a developmental assessment when the child is ~24 months of age. Additionally, a randomly selected 10% of screen negatives from both groups will also be invited to complete this same assessment at ~24 months of age. These assessments will be undertaken by trained researchers who have achieved research-reliable coding on the ADOS-2 as well as having trained on the other measures described below. Parents/caregivers will complete a more detailed general and demographic questionnaire in addition to the following assessments: The ADOS-2 and ADI-R, together with the developmental assessment, and clinical judgement, will be used to determine whether the child meets a DSM-5 diagnosis of ASD.

### Phase 3 – 30-Month Assessment Protocol

Parents/caregivers of all children recruited to both the ASP and SaU arms of the study will complete the preschool version of the Social Responsiveness Scale, Second Edition (SRS-2)(60, 61) when their child is ~30 months of age. The SRS-2 is an autism screening tool that asks parents/caregivers to rate their child's traits of autism, as seen in a naturalistic setting, on a quantitative scale. The total score provides an indication of the extent of social differences. The SRS has good internal consistency (α = 0.93) and good test-retest reliability in preschoolers (intra-class correlation = 0.74) (61, 62).

Parents/caregivers of children identified with a developmental condition from both arms will also complete a semi-structured questionnaire to evaluate the uptake of recommendations, experience of assessment/service use, disability supports, and early intervention received and parental satisfaction with the health and disability services. This will facilitate comparison between those in the ASP arm who received the assessments and recommendations using the NAG and those in the SaU arm who received routine care.

### Phase 4 – Evaluation

GP clinic audits will be conducted to gather data on the number of children in the eligible age group seen during the recruitment period, the number of children where the developmental surveillance was conducted, and the number of children referred for developmental concerns, as per current practice. The data will be obtained using the clinics' client management software to generate deidentified reports on the numbers of children in the eligible age group seen during the recruitment period.

We will conduct qualitative interviews with 10 parent/caregiver and 10 professional (GPs/PNs) participants at each site in order to explore the enablers and barriers for completion of universal developmental and autism surveillance checks within the GP setting as well as about the utilization of the NAG, access to referral pathways and early interventions.

### Data Management

Data will be stored and managed at both sites using two applications – REDCap (Research Electronic Data CAPture) (63, 64) and Salesforce (65).

REDCap is a secure, web-based software platform designed to support data capture for research studies, providing (1) an intuitive interface for validated data capture; (2) audit trails for tracking data manipulation and export procedures; (3) automated export procedures for seamless data downloads to common statistical packages; and (4) procedures for data integration and interoperability with external sources. REDCap servers are located within Australia, thereby ensuring participant data is governed by Australian laws.

Salesforce is a highly secure cloud-based software application designed to store and manage customer data. The application is highly customizable and robust allowing a seamless experience to the end user through automation. The Salesforce database runs on force.com platform, which provides a powerful relational database. Salesforce is compliant with GDPR and Australian Data Privacy laws. It uses industry-accepted encryption products to protect customer data and communications during transmissions between La Trobe University network and the Covered Services, including through Transport Layer Encryption (TLS) leveraging at least 2048-bit RSA server certificates and 128-bit symmetric encryption keys.

Access to the data is restricted to members of the study team, with different levels of access for different members. If families request to complete questionnaires by hard copy, these will be sent to the family, with item level responses and summary and total scores entered in REDCap by the research team.

A unique identifier number for each of the participating children will be generated in REDCap/Salesforce when the parent/caregiver consents to participate in the study. Unique identifiers will also be generated when the SACS Online and ASQ:SE assessments are completed. This data will be assimilated onto the REDCap database and Salesforce database. Data generated at the NSW site will be managed using REDCap and data generated at VIC site will be managed using Salesforce.

### Analytical Plan

#### Sample Size

The total sample size of children recruited into the study will be 2,400 children across the two sites, which will provide adequate statistical power to address the study hypotheses. This sample will enable us to achieve 80% power to detect a difference between the two group means of 0.0935 standard deviations (SD) using a significance level of 0.05. In analyses comparing the smallest anticipated subgroups (as small as 20% of the original group sizes), a mean difference of 0.21 standard deviations will be detectable retaining the same power and significance levels. For the qualitative component of the study, it is envisaged that approximately twenty participants (GPs and PNs) will be enough to obtain thematic data saturation.

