## Abstract

**Background:** The early detection of developmental conditions such as autism is vital to ensure children can access appropriate and timely evidence-based supports, services, and interventions. Children who have undetected developmental conditions early in life are more likely to develop later health, developmental, learning, and behavioral issues, which in turn can have a cumulative effect over the life course.

**Methods:** The current protocol describes a multi-site, cluster randomized control trial comparing a developmental surveillance pathway for autism to usual care, using opportunistic visits to general practitioners (GPs). Units of randomization are GP clinics across two Australian states (New South Wales and Victoria), with thirty clinics within each state, each of which will aim to recruit approximately forty children aged between ~18- and 24-months, for a total of ~2,400 participants. Children will be randomized to two clusters; namely, an autism surveillance pathway (ASP) or surveillance as usual (SaU). The screening process for the ASP arm involves primary and secondary screenings for developmental concerns for autism, using both parent and GP reports and observations. Children in both arms who show signs of developmental concerns for autism will be offered a full developmental assessment by the research team at 24 months of age to determine the efficacy of developmental surveillance in successfully identifying children with autism.

**Trial Registration:** The trial is registered with ANZCTR (ACTRN12619001200178) and reporting of the trial results will be according to recommendations in the CONSORT Statement.

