### Participants and Setting

Within each state (NSW, VIC), approximately thirty GP clinic “clusters” will be recruited (approximately sixty in total). Children aged approximately 18- to 24-months attending the GP clinics will then be recruited as part of each cluster. GP clinics will be recruited through various methods including using Primary Health Networks to distribute study information. GPs and, in some instances, the clinic practice nurse/s (PN) will be recruited, with each clinic having at least one GP consenting to recruit children to the study. A “universal surveillance” approach to recruitment will be implemented, such that any toddler between the eligible ages attending an appointment at the clinic for any reason, including for an immunization, can be recruited to the study. Approximately forty children will be recruited from each GP clinics, creating a total child sample size of ~2,400. For the qualitative component of the study, parents of children identified with a developmental concern and approximately twenty GPs and/or PNs will be recruited.

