### Statistical Analysis

#### Quantitative Analysis

The entire raw dataset will be provided to an independent biostatistician, along with the study protocol and the pre-specified statistical analysis plan, who will conduct an independent analysis of the raw data. Details of this independent statistical analysis, as well as the name and academic institution of the independent statistician and whether compensation or funding was received for conducting the analyses, will be included in the publication of the results of the study.

Descriptive statistics for outcome measures (percentage, mean, and SD) and psychometric properties of the measures (reliability, Cronbach's α) will be reported. Descriptive statistics for all parental socio-demographic will also be presented, with the expectation of no group differences. We will compare the differences between the control arm (SaU) and the intervention arm (ASP) for the following primary outcomes:

(1a). the uptake of autism developmental surveillance as indicated by the proportion of children who participated in the program;(1b). the proportion of children correctly identified by the GPs as being at “high likelihood” of autism, and later confirmed as having ASD through the “gold standard” assessment.(2) the proportion of children in both groups who received referrals following identification of developmental concerns;(3) the access and utilization of child health and developmental services will be ascertained based on the uptake of recommendations as assessed at the 30-month follow up.

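### The stated detectable differences of 0.0935 and 0.21 SD do not follow from 2,400 children, leave no room for clustering by clinic, and are given for means although both hypotheses concern proportions

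*Protocol article*

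**What the plan says.** On power for the hypotheses, the Sample Size section of the protocol article states: "The total sample size of children recruited into the study will be 2,400 children across the two sites, which will provide adequate statistical power". The support offered is "80% power to detect a difference between the two group means of 0.0935 standard deviations (SD) using a significance level of 0.05", together with 0.21 SD at the same power and significance level in "the smallest anticipated subgroups (as small as 20% of the original group sizes". The section gives no intracluster correlation (ICC), design effect, number of clinics, baseline proportion or detectable risk difference.

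Other sections fix the design and the outcomes:

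- **Unit of randomisation (Abstract):** "Units of randomization are GP clinics across two Australian states". Study Design allocates clinics to two arms by minimisation.
- **Cluster number and size (Participants and Setting):** about 30 clinics per state, about 60 in all. "Approximately forty children will be recruited from each GP clinics".
- **Outcomes (Hypotheses; Quantitative Analysis):** both hypotheses are about proportions. Outcome 1a is "the uptake of autism developmental surveillance as indicated by the proportion of children who participated in the program". Outcomes 1b (flagged by the GP and later confirmed as ASD) and 2 (referrals) are also proportions. Outcome 3, access to and use of services, has no stated scale.
- **Analysis (Statistical Analysis):** group differences are to be reported as risk differences with 95% confidence intervals, and the modelling accounts for clustering.

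**The concern.** The power paragraph can be checked against the rest of the article in three ways: whether its figures follow from its own number of children, whether they reflect randomisation of clinics, and whether they are on the scale of the outcomes. It fails all three.

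What is at stake is how the results will be read. GPs and practice nurses carry out the surveillance and make the referrals, so children in one clinic can be expected to resemble each other on these outcomes. A null result, above all on confirmed early identification (1b), could be taken as evidence of no benefit because the trial had been declared adequately powered.

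**Working it through.** **Inputs.** From Sample Size: 2,400 children, 80% power, significance level 0.05, 0.0935 SD, 0.21 SD, subgroups of 20%. From Participants and Setting: about 60 clinics of about 40. Assumed because not stated: 1:1 allocation (1,200 per arm), a two-sided test, and the ICC.

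**1. Reproducing the stated figures with no clustering.** Detectable difference in SD units = (1.960 + 0.842) × √(2/n), with n per arm.

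| Total children | n per arm | Detectable, whole sample | n per arm in 20% subgroup | Detectable, subgroup |
|---|---|---|---|---|
| 2,400 | 1,200 | 0.114 SD | 240 | 0.256 SD |
| 3,600 | 1,800 | 0.0934 SD | 360 | 0.209 SD |
| Stated | | 0.0935 SD | | 0.21 SD |

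At 1,200 per arm, power at 0.0935 SD is Φ(0.0935/√(2/1200) − 1.96) = 63%. Power at 0.21 SD in the subgroups is also 63%.

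Variants tried:

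- One-sided 0.05 gives 0.102 and 0.227 SD, still larger than stated.
- Reaching 0.0935 SD needs 3,592 children two-sided or 2,830 one-sided. Allocation of 2:1 needs more (4,041 two-sided).
- The exact t calculation gives the same 63%.

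The design effect that would make 0.0935 SD correct with 2,400 children is 1,200/1,796 = 0.67. A positive within-clinic correlation gives a design effect above 1, so no allowance for it can be in the figure.

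**2. Adding the clusters.** Design effect DE = 1 + (40 − 1) × ICC. Detectable difference = 2.802 × √(2 × DE/1200). Power at 0.0935 SD = Φ(0.0935/√(2 × DE/1200) − 1.96). The last column multiplies the SD figure by √(0.5 × 0.5) = 0.5.

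| ICC (assumed) | DE | Effective total | Detectable | Power at 0.0935 SD | Points near 50% |
|---|---|---|---|---|---|
| 0.01 | 1.39 | 1,727 | 0.135 SD | 49% | 6.7 |
| 0.02 | 1.78 | 1,348 | 0.153 SD | 40% | 7.6 |
| 0.05 | 2.95 | 814 | 0.196 SD | 27% | 9.8 |
| 0.10 | 4.90 | 490 | 0.253 SD | 18% | 12.7 |

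These use the normal approximation. Using t with 58 degrees of freedom makes them slightly larger (0.137 SD at ICC 0.01, 0.258 SD at 0.10).

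**3. Uptake (1a).** Starting from the 30% attendance that the Introduction gives for New South Wales, the rise detectable with 80% power is 6.3, 7.2, 9.3 and 12.1 points at the same four ICCs. An assumed 20-point rise would have over 99% power at ICC 0.10 and about 93% at ICC 0.20.

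**4. Confirmed identification (1b).** The ASD prevalence p implied by the SACS properties under Measures (sensitivity 82–84%, specificity 99–99.8%, PPV 81–83%) is PPV × (1 − sp) / [se × (1 − PPV) + PPV × (1 − sp)]. This is 1.0–1.2% at specificity 99.8% and 4.8–5.6% at 99%. Take 83% of children with ASD flagged in the pathway arm (assumed, near SACS sensitivity), an assumed share flagged in usual care, and confirmed cases per recruited child as the outcome. Power is then:

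| Usual-care detection (assumed) | Prevalence 1% / 2% / 5%, no clustering | Prevalence 1% / 2% / 5%, DE 1.39 |
|---|---|---|
| 40% | 27 / 48 / 86% | 21 / 37 / 74% |
| 20% | 58 / 86 / >99% | 45 / 74 / 99% |
| 10% | 75 / 96 / >99% | 61 / 89 / >99% |

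At 40% detection and 1% prevalence the comparison rests on about 1,200 × 0.01 × 0.83 = 10 events against 1,200 × 0.01 × 0.40 = 5.

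**The case against.** Several objections have force and limit the point.

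- **The analysis accounts for clustering.** This stands. The omission is in the power statement and does not in itself threaten the type I error of the planned analysis.
- **The hypotheses name no effect size.** This stands. A reader might infer that the trial is underpowered for its hypotheses, but what fails is 80% power for 0.0935 SD. For uptake, differences of roughly 6 to 13 points remain detectable over the ICC range shown.
- **Power for 1b depends on what is assumed for usual care.** This stands. At 1% prevalence without clustering it moves from 27% to 75% as assumed detection falls from 40% to 10%. The pathway's full flagging rule is also wider than SACS alone, so its detection could exceed 83%. Still, no scenario shown at 1% prevalence reaches 80%.
- **An SD difference converts to points for a mid-range proportion.** This holds for 1a (0.0935 SD is about 4.7 points near 50%). It does not help with a rare outcome such as 1b.
- **A baseline covariate could reduce the variance.** A correlation of about 0.58 would reproduce both stated figures under independence. The Sample Size section mentions none.
- **An article condenses the full protocol.** That would excuse missing detail. It does not excuse figures that contradict the sample size printed beside them.

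Four further readings go too far. The figures are not simply those of 2,400 independent children, because they match about 3,600. That 3,600 was once the target is only an inference from the arithmetic. Not every primary outcome is a proportion, since outcome 3 has no stated scale. Nor do the documents show that clinic is the dominant source of variance: with 40 per clinic, the between-clinic share of an arm mean's variance, 40 × ICC/DE, is 29% at ICC 0.01 and 45% at 0.02.

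**Conclusion.** The power statement is wrong as written. Under 1:1 allocation and a two-sided 0.05 test, 2,400 independent children detect 0.114 SD rather than 0.0935, and 0.256 SD rather than 0.21 in the 20% subgroups. One-sided testing does not rescue either figure. This part needs no assumption about clustering.

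For the design described, about 60 clinics of about 40, power at 0.0935 SD is 49% to 18% over ICCs of 0.01 to 0.10. That range is assumed, as the document gives no ICC.

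Because the statement is also on a scale that neither hypothesis uses, the claim of adequate power is unsupported by the calculation given. It is not shown to be false: uptake may be well powered, and 1b may or may not be, depending on prevalence and usual-care detection.

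**What to change.** Keep 60 clinics of 40 children and rewrite the Sample Size paragraph:

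1. Correct 0.0935 and 0.21 SD, stating allocation and sidedness.
2. For 1a, give the detectable risk difference with 60 clinics of 40 over a stated ICC range (for example 0.01 to 0.10), with the design effect shown.
3. For 1b, give power separately, as confirmed true positives per recruited child, over stated ranges of ASD prevalence and usual-care detection.
4. Limit the adequacy claim to the hypotheses for which these figures meet it.

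The cost is wording and less favourable stated figures. No extra clinics or children are needed.

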## Methods and Analysis

### Study Design

A multi-site, cluster RCT with a qualitative component will be implemented (Figure 1). Using a minimization randomization procedure over size of GP clinic (<4 GPs or ≥4) and site (NSW or VIC), the participating GP clinics within the two Australian States (NSW and VIC) will be allocated to one of two arms:

Surveillance as Usual (SaU), representing current practice, orASD surveillance pathway (ASP), which will implement the “enhanced surveillance” protocol.

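### The detectable differences of 0.0935 SD and 0.21 SD do not follow from 2,400 children; they match about 3,600, and power at 2,400 is about 63%, not 80%

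*Protocol article*

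**What the plan says.** The protocol article gives the sample in two places. Participants and Setting describes about sixty clinics with about forty children each, "creating a total child sample size of ~2,400". Sample Size repeats it: "The total sample size of children recruited into the study will be 2,400 children across the two sites".

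Sample Size then makes the article's only quantitative power statement. For the whole sample: "This sample will enable us to achieve 80% power to detect a difference between the two group means of 0.0935 standard deviations (SD" units, "using a significance level of 0.05". For the smallest subgroups, taken as 20% of the original groups: "a mean difference of 0.21 standard deviations will be detectable retaining the same power and significance levels".

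Under Study Design, clinics "will be allocated to one of two arms". The article does not state the allocation ratio or whether the test is one- or two-sided. The Sample Size section mentions no covariate adjustment, intraclass correlation or design effect. Quantitative Analysis plans 95% confidence intervals for the group comparisons, which fits two-sided testing at 0.05.

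**The concern.** A difference of 0.0935 SD is small for a comparison of 1,200 with 1,200 at 80% power, so the standard formula should be checked against it. If it fails, the article's only numerical justification of the sample is wrong for the sample the trial will recruit. Readers would believe that the chance of missing a true difference of 0.0935 SD is 20% when it is nearer 37%. A null result, above all in a subgroup, could then be read as ruling out effects that the trial was not powered to detect. The protocol also goes to the independent biostatistician, so the figures could pass into the results paper.

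**Working it through.** **Inputs**
- Total 2,400 children (Participants and Setting; Sample Size).
- Two arms (Study Design). The ratio is not stated; 1:1 is assumed, giving 1,200 per arm. This is the most favourable case.
- Level 0.05 and power 80% (Sample Size). Two-sided is the base case; one-sided is also tried.
- Subgroups of 20%: 0.2 × 1,200 = 240 per arm.
- Differences are in SD units, so SD = 1.

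**Formulas** (comparison of two means, normal approximation, n per arm)
- Detectable difference: d = (z_alpha + z_power) × √(2/n), with 1.960 + 0.842 = 2.802 for a two-sided test.
- Power at d: Φ(d/√(2/n) − z_alpha).
- Sample size per arm: n = 2 × 2.802²/d².

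**Attempt to reproduce the printed figures, two-sided**

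| n per arm | Total or share | Detectable d at 80% | Printed d | Power at printed d |
|---|---|---|---|---|
| 1,200 | 2,400 | 0.114 | 0.0935 | 62.9% |
| 240 | 20% of 1,200 | 0.256 | 0.21 | 63.3% |
| 1,800 | 3,600 | 0.0934 | 0.0935 | 80.1% |
| 360 | 20% of 1,800 | 0.209 | 0.21 | 80.4% |

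Power in the first row: 0.0935/√(2/1,200) = 2.290; 2.290 − 1.960 = 0.330; Φ(0.330) = 0.629. An exact t-test calculation agrees (62.9% overall, 63.2% in the subgroup).

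Solving for the sample, 0.0935 SD needs 1,796 per arm, or 3,592 in total, and 0.21 SD needs 356 per arm. Relative to the printed values, the differences detectable with 2,400 are larger by 0.1144/0.0935 = 1.22 and 0.2557/0.21 = 1.22.

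**Other readings tried at 2,400**
- One-sided 0.05: detectable differences 0.102 and 0.227 SD; power at the printed differences 74.1% and 74.4%; total needed for 0.0935 SD is 2,830. Neither figure is reproduced.
- Allocation 2:1 (1,600 and 800): 2.802 × √(1/1,600 + 1/800) = 0.121 SD, further away.
- One-sample formula: 0.057 SD with n = 2,400 and 0.081 SD with n = 1,200. No match.
- Covariate adjustment: to bring 0.1144 down to 0.0935, covariates would have to explain 1 − (0.0935/0.1144)² ≈ 33% of the outcome variance. No such assumption is stated.

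**Effect of clustering.** With 40 children per clinic the design effect is 1 + 39 × ICC. The article gives no ICC, so the values below are assumptions.

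| ICC (assumed) | Design effect | Detectable d, 2,400 children | Power at 0.0935 SD |
|---|---|---|---|
| 0.001 | 1.039 | 0.117 | 61% |
| 0.01 | 1.39 | 0.135 | 49% |
| 0.02 | 1.78 | 0.153 | 40% |
| 0.05 | 2.95 | 0.196 | 27% |

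**The case against.** Nobody can rescue the arithmetic from the stated inputs; the case on the other side is about what may be read into it.

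- **The 3,600 origin is inference.** The article never mentions 3,600 children. The second match is also not independent of the first, because 0.0935/√0.2 = 0.209: the subgroup figure is the overall figure rescaled. This stands. The match suggests figures carried over from a larger planned sample, but it does not prove it, and the error does not depend on how it arose.
- **Sidedness is not stated.** This stands in part. A one-sided test would give about 74%, still short of 80%, and the planned 95% intervals point to two-sided testing.
- **Covariate adjustment could close the gap.** The analysis section does plan adjustment for variables strongly associated with outcome. But the power statement describes a plain difference between two means and claims no reduction in variance, so this does not explain the figure.
- **The corrected figures are themselves optimistic.** True. Clinics are randomised, so 0.114 and 0.256 SD are only a starting point.
- **The practical consequence is limited.** The listed primary outcomes are mainly proportions, to be compared as risk differences, so a standardised mean difference is not their natural effect measure. Recruitment and analysis do not change either. This bears on how far the statement informs readers. It does not make the statement correct.

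**Conclusion.** The power statement is wrong as written. For 2,400 children in two equal arms, with a two-sided 0.05 test and no clustering or losses, the differences detectable with 80% power are 0.114 SD overall and 0.256 SD in 20% subgroups. Power at the printed 0.0935 and 0.21 SD is about 63%, or about 74% under a one-sided test. The stated overall difference would need about 3,590 children two-sided. Equal allocation is the most favourable ratio, and any positive intraclass correlation or loss to follow-up lowers power further, so 63% is the best case for the two-sided test. The assumptions not taken from the article are the 1:1 ratio and the two-sided test; changing either does not restore 80%. That the figures come from a 3,600-child plan is a plausible reading only.

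**What to change.** Correct the Sample Size section so that the total and the detectable differences agree.

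1. If 2,400 is the intended sample, replace 0.0935 with 0.114 SD and 0.21 with 0.256 SD, labelled as values for individual randomisation.
2. State the sidedness and the allocation ratio.
3. State an intraclass correlation with its source, apply the design effect for about forty children per clinic, and give the resulting figures as the trial's detectable differences. The uncorrected values should not stand alone.
4. If a larger sample was intended, correct the total wherever it appears.
5. Do not carry 0.0935 and 0.21 into the results paper, and correct them in the analysis plan if they appear there.

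Restating the figures means changing two numbers and adding a sentence or two of assumptions. Recruitment and analysis are unaffected; the cost is a less favourable statement of what the trial can detect. Raising the total instead would change recruitment.
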